#### Residential, community and sociodemographic data

Characteristics of each participant dwelling as well as the outdoor environment that might affect building temperatures (building density, landcover, nearby water bodies, trees, and other shading) will be surveyed and assessed using a combination of geospatial and ground survey data. Features of the residence that will be measured include dimensions, presence of windows and doors, materials of floors, walls, ceilings and roofs, and ventilation.

Key to the success of the heat adaptation interventions is an assessment of affordability and feasibility in local-contexts, therefore comprehensive socio-economic and demographic information will be collected and considered in the evaluation. A study-specific demographic and socio-economic survey which is currently being used in the ongoing studies, and has been shown to be culturally appropriate, will be employed.

### Data management

Quantitative data from multiple sources will be collated and stored in a secure relational database hosted at the University of Cape Town. Personal identification information will be removed, and data will be merged and stored using alphabetic-numerical identification codes to maintain participant anonymity. The data base will be password protected and available to the research team exclusively. Qualitative data will be stored as anonymised transcripts.

All environmental data will be archived on the University of Cape Town’s open data repository, ZivaHub [66], which is driven by Figshare. All data are easily locatable by searching within the platform, and through general internet searches. All datasets will have a persistent DOI which will be used to identify associated publications, raise awareness of the availability of the data, and facilitate searching. Project data will be available on request under a data sharing agreement that provides commitments to: 1) using the data only for research purposes and not to identify any individual participant; 2) securing the data using appropriate computer technology; and 3) destroying or returning the data after analyses are completed. After the project is complete, data will be freely available for use (CC-BY licence), except where there is ongoing analysis of the data for a specific output by the project team. All data will be fully accessible 12 months after the project completion, once all publications have been submitted. In the final year of the project, the HABVIA team will publish a short article, describing the dataset in Wellcome Open Research to help researchers discover, access, and reference the resource.

### Data analysis

For the statistical analysis, means and standard deviations will be presented for continuous variables; medians and interquartile ranges will be reported for continuous variables with asymmetrical distributions. Continuous variables with a small number of ordered categories, as well as all nominal variables, will be described with counts and percentages.Objective 1. The effect of ambient outdoor and indoor temperature on physiological health outcomes (primary: sleep; secondary: core body temperature, hydration) will be assessed both cross-sectionally and longitudinally using a univariable and multivariable generalized linear mixed model. For the multivariable model we will adjust for environmental conditions (humidity, cloud cover, wind speed, precipitation); health covariates (body composition, blood pressure, physical activity, glucose); participant characteristics (sex, age); household characteristics (roof and wall type; size) as well as differences between sites (country, rural vs. urban).Objective 2. The impact of the interventions will be tested in phases, first the association between intervention exposure and night-time indoor temperature, adjusting for household characteristics, site and intervention type. Secondly, the association between intervention exposure and sleep, our primary outcome as well as secondary physical and mental health outcomes. The mediating effect of night-time indoor temperature on this association will be investigated, while adjusting for the covariates described under Objective 1). In addition to this, structural equation modelling (SEM) will be used to produce a pictographic representation of a-priori determined relationships between the variables of interest. It does this by estimating path equations simultaneously allowing for the calculation of direct, indirect and total effects. For missing data, we will explore different imputation methods and run sensitivity analyses to explore whether participants lost to follow-up differ when compared to those who completed the study measurement periods.Objective 3. Qualitative data analysis will be done in parallel with the community engagement workshops and Focus Group Discussions, allowing emerging analysis to shape subsequent implementation and data collection procedures. The analysis will answer process evaluation questions and draw on various qualitative methods including but not limited to reflexive thematic analysis and codebook analysis. A qualitative analysis software (such as MAXQDA) will be used by the investigators to facilitate coding, data management, and data interpretation.

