### Study aims and objectives

The HABVIA study aims to address some of the large evidence gaps in human health and wider social outcomes of heat adaptation in SSA, namely (i) the paucity of data from well-designed heat adaptation intervention trials in real-world high-vulnerability settings in the region and (ii) the absence of quantitative measurements of the health outcomes of these interventions. HABVIA aims to achieve this by identifying and implementing socially and culturally acceptable, affordable, and scalable heat adaptations for housing in low-income informal settlements in four communities in Ghana and South Africa.

Specifically, the following three objectives will be addressed:*Objective 1*. To explore the physiological response to extreme heat by quantifying the relationship between high seasonal ambient temperatures and humidity, and objectively measured health outcomes (primary: sleep; secondary: core body temperature, hydration) over three hot seasons in two rural and two urban African settings.*Objective 2*. To investigate any effects of passive-cooling interventions in lowering night-time indoor temperature and improving physical and mental health metrics, compared to controls.*Objective 3*. To determine the feasibility and social acceptability of such passive cooling adaptation interventions in climate vulnerable communities.

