### Study design

HABVIA is a parallel-group controlled trial evaluating heat adaptation options in four sites, one urban and one rural low-income community each in Ghana and South Africa (SA), respectively. Participants will be assigned to intervention or control group using 1:1 block randomisation per site, with an equal distribution of male/females. An automated, computer-generated algorithm will be used for randomisation. Due to the logistical constraints of implementing adaptations in low-income settings, a building verification survey will be conducted to identify residences where the passive cooling interventions cannot be feasibly implemented. These participants will be automatically assigned to the control group and receive an alternative adaptation at the end of the study. Due to the nature of the interventions, participants and researchers will not be blinded to the intervention allocation. There are no pre-defined specific criteria for discontinuing the allocated interventions, but reasons for withdrawal will be tracked and reported in subsequent publications and taken into consideration for analysis.

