**Fig. 2 Fig2:**
[figure not shown]
Schedule of enrolment, interventions, and assessments

The measurement of health outcomes will occur over three consecutive hot seasons, (November to March) with one baseline collection during the 2023 - 2024 hot season and two subsequent post-intervention data collection periods (2024 - 2025 and 2025 - 2026). The interventions will be identified by the study team and presented to the participants during a series of workshops following the baseline measurements in year 1. The adaptation will be implemented following the baseline data collection in year 1, and prior to the start of year 2 hot-season data collection period. For each hot season monitoring period, participants at each site will be grouped into six equal groups of *n*= 10 and monitored for three non-consecutive one-week periods, over 16-week hot season. We have accounted for approximately 4-weeks of suspended research activities during December and January months due to local holidays (Fig. 3). The 7-day health measurement period will include an initial clinic visit (lasting approximately 3 hours) followed by six consecutive 24-hour periods of off-site physiological data acquisition.

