**Fig. 3 Fig3:**
[figure not shown]
Measurement schema for physical health data collection over three hot seasons. There will be 60 subjects in each site, 30 intervention and 30 control. These will be split into 6 subgroups, each of which is monitored over three 7-day periods, evenly spaced over the hot season

Throughout the 16-week hot season, indoor temperature and humidity data will be recorded continuously, while external climate data will be collected continuously throughout the year with the data being provided to the research team by various meteorological agencies, supplemented by project installed weather stations (also see Environmental data, below).

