#### Environmental data

Indoor temperature and humidity will be recorded continuously at 30-minute intervals, using a fixed hygrochron sensor (model DS1923-F5# iButton, Maxium Integrated, CA, USA) installed in the main sleeping area. External meteorological data including temperature, humidity, wind speed, sunshine, cloud cover, and rainfall will be collected and analysed as a control for internal conditions as well as to establish long-term temperature (and other climate variables) statistics and trends.

For three of the study sites, this data will be provided by the South African Weather Services (SAWS) and Ghana Meteorological Agency who operate Automatic Weather Stations in the vicinity. For the remaining rural site in Kumasi, a cellular wireless weather station (model WS-WH- 6006, Ecowittt, HK) was installed at a height of 6.85 m above ground, in the village. The installation height was elevated above the standard 2 m [65] at the request of the chief, to mitigate the risk of potential damage. The wireless outdoor sensor includes a solar-powered multi-sensor array (rain gauge, thermo-hygrometer, wind direction/speed sensor, and UV light sensor), as well as an indoor temperature sensor which communicates using cellular network connection to a receiver unit. Data will be stored on an SD card.

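### Objective 1 pools three hot seasons, two of them after about half the homes are modified, but its stated covariate list omits intervention status and season, so the temperature-sleep slopes may be biased or hard to interpret

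*Protocol article*

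**What the plan says.** Study aims and objectives sets Objective 1 as the relation of seasonal heat and humidity to measured health outcomes, sleep being primary, "over three hot seasons in two rural and two urban African settings". Research procedures gives the calendar: "one baseline collection during the 2023 - 2024 hot season and two subsequent post-intervention data collection periods". On installation it says: "The adaptation will be implemented following the baseline data collection in year 1, and prior to the start of year 2 hot-season data collection period". The caption to Fig. 3 gives the planned split: "There will be 60 subjects in each site, 30 intervention and 30 control".

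Data analysis states that "The effect of ambient outdoor and indoor temperature on physiological health outcomes" will be examined cross-sectionally and longitudinally with univariable and multivariable generalised linear mixed models. It then lists the adjustment set:

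- weather: humidity, cloud cover, wind speed, precipitation
- health: body composition, blood pressure, physical activity, glucose
- person: sex, age
- dwelling: roof and wall type, size
- site: country, rural or urban

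Intervention group, installation status and season or year are not on the list. Objective 1 is not limited to the baseline season or to control homes. Intervention exposure enters a model only under Objective 2.

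**The concern.** From the second season the intervention is meant to lower indoor temperature in the allocated homes. The trial is open-label, so it may also change sleep by routes that the indoor sensor does not record, such as expectation, ventilation, light or noise. If so, intervention status influences both the indoor exposure and the outcome, and leaving it out pushes part of its effect into the temperature slope. A participant random intercept would not remove this, because status changes within a person between seasons one and two.

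The outdoor slope raises a different problem. A home modification cannot alter outdoor temperature, but it can alter how much outdoor heat reaches the sleeper. A single pooled slope then mixes two kinds of home.

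Season matters because the project itself changes over time (workshops between measurement periods, heat advisories, new recruits in year 2) while the seasons may differ in heat. At stake is the estimate for the first stated objective and its primary outcome. The randomised comparison under Objective 2 is not affected.

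**Working it through.** **Inputs from the protocol.** Four sites of 60 give 240 participants, half allocated to intervention. There are three seasons, two of them after installation, with three monitored weeks per season. The Sample size calculation section pairs 4.3 °C with 11.6 minutes of sleep. The protocol states no slope for Objective 1, so the reference is 11.6/4.3 = 2.70 min/°C (negative in sign: less sleep with more heat).

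**Share of data under intervention.** Planned person-weeks: 240 × 3 × 3 = 2,160. Under intervention: 120 × 2 × 3 = 720, a fraction p = 1/3, so p(1 − p) = 2/9.

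**Indoor slope, by formula.** Shift = direct effect × cov(status, T)/var(T). Assumptions, none from the documents: cooling of 2 °C, a direct gain of 5 minutes of sleep, and a variance of T apart from the intervention of 4 or 9 °C².

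- cov = −2 × 2/9 = −0.444
- var(T) = 4 + 2² × 2/9 = 4.89, or 9 + 0.89 = 9.89
- shift = 5 × (−0.444)/4.89 = −0.45 min/°C, or 5 × (−0.444)/9.89 = −0.22 min/°C
- relative to 2.70: 17% or 8% too steep; doubled for a 10-minute direct effect; zero for no direct effect

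This is a one-predictor formula and ignores the planned covariates and random effects.

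**Indoor slope, by simulation.** The set-up was 240 people × 9 weeks with a random intercept, site terms in every model, a true slope of −2.70, and 60 simulated trials per scenario. Assumed sleep SDs were 40 min between and 30 min within persons. The adjusted model adds group, season and group by post-installation. In the rows below, seasons do not differ and the outdoor-to-indoor pass-through is unchanged.

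| Cooling | Direct effect | Slope, terms omitted | Slope, adjusted |
|---|---|---|---|
| 2 °C | 0 min | −2.73 | −2.72 |
| 2 °C | 5 min | −2.93 | −2.65 |
| 4.3 °C | 5 min | −3.05 | −2.65 |
| 4.3 °C | 10 min | −3.52 | −2.68 |

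At 2 °C and 5 minutes the gap is 2.93 − 2.65 = 0.28, inside the formula's range. The shift is not always steeper. With 4.3 °C cooling, no direct effect, later seasons 1 °C warmer and 5 minutes less sleep in those seasons, the slope with terms omitted is −2.44, against −2.72 adjusted.

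**Outdoor slope.** Suppose pass-through falls by 30% in modified homes (assumed). The pooled slope is then 2.70 × (1 − 0.30 × 1/3) = 2.43 in size. The simulation gives −2.43 at 4.3 °C cooling with equal seasons, and −2.70 for unmodified homes once status and its temperature interaction are included. If cooling is a constant shift and seasons are equally hot, the pooled slope is −2.70. If later seasons are also 1 °C warmer, the 30% case becomes −2.08, because the calendar then links status to outdoor heat.

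**Across all scenarios.** With the terms omitted, the indoor slope ran from −2.38 to −3.63 and the outdoor slope from −1.77 to −2.95. Adjusted, both stayed between −2.60 and −2.80. These ranges reflect the assumed inputs and some simulation noise; they are not forecasts.

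**The case against.** The strongest reply is that a condensed article leaves time terms, random effects and scaling to a fuller document, that a longitudinal analysis may imply a time term, and that a cross-sectional analysis of the baseline season would be free of intervention. Part of this stands: the fuller plan may add the terms. But the article fixes an itemised list and reuses it for Objective 2, names no time term, and does not say which season the cross-sectional analysis uses.

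Second, Objective 2 already plans mediation by night-time indoor temperature and a structural equation model with direct and indirect effects. That does separate the paths for indoor temperature. It does not correct the Objective 1 estimate, and it offers nothing for outdoor temperature. It also shows that the plan allows for a direct effect, which the Objective 1 model implicitly sets to zero.

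Third, roof and wall type could absorb part of a roof or wall modification if recorded again after installation. The protocol does not say that they will be.

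Fourth, season is a judgement. Season terms remove between-season heat contrasts, which belong to the question. This stands and shapes the fix.

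A reader might also infer that pooling sites confuses site with heat, or that the raised weather station ("The installation height was elevated above the standard 2 m [65] at the request of the chief") distorts the outdoor slope. The documents do not support making this part of the point. The four sites are the two-by-two of country and rural or urban, and both factors are in the multivariable model. They absorb most site differences, or all with their interaction, and a constant height offset is itself a site-level difference. Nothing in the text calls for centring temperature on this account.

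**Conclusion.** The omission is real as written and worth correcting. Its consequence is conditional. The indoor slope is biased if the intervention affects sleep outside measured indoor temperature, or if seasons differ in both heat and sleep. It is unbiased if neither holds. The outdoor slope, where pass-through changes, is an average over modified and unmodified homes. That is effect modification, not confounding by the intervention.

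A reader might infer that Objective 1 will necessarily re-report the intervention effect as a temperature effect. The documents do not support that: they give no direct effect, no standard deviations and no season differences. About 0.2 to 0.45 min/°C against 2.7 is an illustration resting on 2 °C of cooling, a 5-minute direct effect and temperature variances of 9 and 4. The one-third exposure share rests on the planned 30/30 split, which may shift because of the rule for infeasible homes: "These participants will be automatically assigned to the control group and receive an alternative adaptation at the end of the study". Objective 1 is also framed as exploratory, which limits the weight of the point.

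**What to change.** In the Objective 1 longitudinal model, add time-varying intervention status (group by post-installation, with group as a main effect) and its interaction with temperature, so that slopes for unmodified and modified homes can be reported separately. Report the model with and without season, and say that season terms remove between-season heat contrasts. Add a sensitivity analysis on intervention-free data: all participants in year 1 plus controls in years 2 and 3.

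The cost is wording and a few model terms; no new data are needed. The restricted analysis drops about 720 of 2,160 planned person-weeks, leaving 1,440. Its later seasons also over-represent dwellings moved to control because the intervention was not feasible there, which ties calendar time to housing type. That is why it serves better as a sensitivity analysis than as the main model.

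### The covariate lists stated for Objective 2 omit outdoor temperature, hot season and the pre-intervention value; this mainly costs precision, but becomes bias in three identifiable places

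*Protocol article*

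**What the plan says.** The Data analysis section of the protocol article sets out Objective 2 in phases. The first is described as "first the association between intervention exposure and night-time indoor temperature, adjusting for household characteristics, site and intervention type". The second relates intervention exposure to sleep and to the secondary physical and mental health outcomes, and then examines mediation by night-time indoor temperature "while adjusting for the covariates described under Objective 1".

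For Objective 1 the plan says "we will adjust for environmental conditions (humidity, cloud cover, wind speed, precipitation"; health covariates, sex, age, household characteristics, country and rural or urban setting follow. The Objective 1 exposure is temperature itself: "The effect of ambient outdoor and indoor temperature on physiological health outcomes".

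The Environmental data section says that external meteorological data, temperature included, "will be collected and analysed as a control for internal conditions as well as to establish long-term temperature" statistics. Table 1 lists outdoor air temperature as continuously recorded. Research procedures describes "one baseline collection during the 2023 - 2024 hot season and two subsequent post-intervention data collection periods". It also says that "participants at each site will be grouped into six equal groups of" ten, each monitored in three separate weeks per season. Study design assigns participants 1:1 within site, except that homes where the intervention cannot feasibly be installed go to control.

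**The concern.** Temperature is rightly not a covariate in Objective 1, because it is the exposure there. When Objective 2 takes over the same list by cross-reference, it inherits humidity, cloud, wind and rain, but not the weather variable most directly tied to indoor temperature. The first-phase list has no weather variable at all, which does not match the stated use of external data as a control. Neither list has a season term or the pre-intervention value, although a whole season is measured before installation.

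Three things are at stake. Precision is lost. The indoor-temperature-to-sleep path in the mediation model is left open to confounding by outdoor heat. Differences that existed before installation, in homes that reached the control group without randomisation, are not corrected by those homes' own earlier measurements.

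**Working it through.** **Named terms, side by side.** First phase: household characteristics, site, intervention type. Mediation: the Objective 1 list. Outdoor temperature, season and pre-intervention value appear in neither. All three are available from Table 1 and Research procedures.

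**Precision.** The plan gives no figure to reproduce on this point. Its 24 per group cannot be re-derived because no SD is stated; at two-sided 0.05 and 80% power it implies a standardised difference of about 0.81. It serves below only as a yardstick. Let r be the correlation between baseline and follow-up. The documents do not give it; the range 0.3 to 0.7 is an assumption.

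- One follow-up value, baseline-adjusted: variance factor 1 − r². For r = 0.3, 0.5, 0.7 this is 0.91, 0.75, 0.51, a cut of 9%, 25%, 49%. Twenty-four per group then behaves like 24/0.91 = 26, 24/0.75 = 32, 24/0.51 = 47.
- Mean of two follow-up seasons, equal correlations: [(1 + r)/2 − r²] / [(1 + r)/2] = 0.56/0.65 = 0.86, 0.50/0.75 = 0.67, 0.36/0.85 = 0.42.

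These factors need a shared expected baseline in the two arms. If each arm keeps its own baseline mean and the estimate is a difference in change, the variance is (1 + r)/2 + 1 − 2r = 1.5(1 − r). Relative to (1 + r)/2 that is 1.05/0.65 = 1.62, 0.75/0.75 = 1.00, 0.45/0.85 = 0.53: a gain only when r exceeds 0.5.

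**Weather, concurrent comparison.** If the post-installation seasons are compared between arms within site, both arms share the same weather and there is no systematic bias. For the staggered health outcomes, the roster may be unbalanced by arm. With 30 and 30 people allocated at random over six subgroups of ten, 20,000 simulated allocations gave an arm difference in weather with mean 0 and SD about 0.24 of the between-subgroup weather SD per site. That is noise.

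**Weather, pooled seasons.** Suppose all three seasons enter with exposure coded 0 before and 1 after installation in the intervention arm, a random participant effect and no season term. If both later seasons differ from baseline by one unit for everyone, the exposure coefficient absorbs (1 + 2r)/(2 + r) units, where r is now the within-person correlation. For r = 0, 0.3, 0.5, 0.7 this is 0.50, 1.6/2.3 = 0.70, 2.0/2.5 = 0.80, 2.4/2.7 = 0.89. With a group main effect added it is 1.0. With a season term it is 0 in every case.

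**Mediation.** Randomisation protects the path from intervention to indoor temperature, but not the path from indoor temperature to sleep. Outdoor heat raises indoor temperature, and Background and rationale says that daytime heat exposure carries over to disturb sleep. A model without outdoor temperature credits part of that second route to indoor temperature. If hotter days shorten sleep independently, the indirect effect is overstated.

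**Non-randomised controls.** Infeasible homes go to control because of how they are built. Roof, wall and size covariates are proxies for that difference; the home's own pre-installation indoor temperature measures it directly.

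**The case against.** The strongest defence is that absence from a covariate list is not absence from the model. The abstract plans generalised linear mixed models and the Discussion plans longitudinal as well as cross-sectional group comparisons. Such models could carry the baseline season as a repeated outcome. That stands: the plan is not shown to discard baseline data. Nor does it ignore outdoor temperature altogether, since the Environmental data section commits to using it.

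A reader might infer that weather is generally mixed into the intervention effect. The documents do not support this. Controls are concurrent within site, and the pooled model that would produce season bias is possible but never stated. A reader might also infer that staggered weeks distort the first phase. They do not: indoor temperature is logged every 30 minutes throughout the hot season, so arms can be compared on the same nights. Replacing site by country and rural or urban setting is also minor; the four sites are the cells of that two-by-two layout, so at most one interaction term is missing.

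Finally, this is a condensed article, and a separate analysis plan may hold the detail. That would answer a complaint about silence. Here the article states specific lists, and they do not match its own statement about external data.

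**Conclusion.** The point holds in a limited form. The stated Objective 2 lists omit three terms that the trial measures, and the Data analysis and Environmental data sections need reconciling. For the total effect between concurrent arms, the main consequence is lost precision: about 9% to 49% of the variance for an assumed correlation of 0.3 to 0.7, relative to an analysis that makes no use of baseline. The gain over the intended mixed model could be smaller, because the article does not say how that model treats the baseline season.

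Bias is a concern in three places only: the mediation analysis and the structural equation model; the contrast involving homes assigned to control for infeasibility; and any model pooling the baseline season with a time-varying exposure and no season term, where half or more of a season shift would enter the effect. The sizes of the first two cannot be computed from the document. The change should be made before analysis, particularly since the trial is unblinded and later covariate choices would be hard to defend.

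**What to change.** Carry the external-weather control into the Objective 2 text. For both phases, specify a longitudinal mixed model over all three seasons with season, group by post-installation season, site at four levels, same-night outdoor temperature and humidity, and a random participant effect.

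Enter the baseline season as a repeated outcome, not as a covariate. Participants and enrolment allows recruitment in year 2, and those people have no baseline-season value; a baseline covariate would drop them or require imputation.

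Do not force a common baseline mean on homes assigned to control without randomisation; give them their own. A common mean for the remaining homes, which is what secures the precision gain, is justified only if feasibility was judged in the same way whatever the allocation. The article does not give the order of survey and randomisation, so this should be stated, and each control home's route of assignment recorded.

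Include outdoor temperature as a mediator-outcome confounder in the mediation model and the structural equation model. Where monitoring rosters are still open, balance the subgroups of ten by arm for the staggered health outcomes.

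The cost is a few more model terms, a flag for route of assignment and, where still possible, a balanced roster. No new measurements are required.
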